### **Specific objectives:**

- 1) To determine the sociodemographic factors and clinical variables among study population.
- 2) To determine the prevalence of future vaccination uptake following the InTroDuce-Programme.
- 3) To evaluate the level of participants' attitudes and barriers towards future vaccination uptake before and after the InTroDuce-Programme.
- 4) To determine the effectiveness of the InTroDuce-Programme in improving knowledge and future uptake of influenza and Tdap vaccination among pregnant mothers.
- 5) To determine the factors associated with low future uptake of vaccine with socio-demographic factors (age, race, income, education) among pregnant mothers.

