### 3.4 Sample Size

The sample size was calculated using openEpi software based on earlier study which demonstrated proportion of 55% in intervention group (website with vaccine information) and 36% in control group (usual care) (14) The final sample size is 351 based on the design effect of 1.3, 20% of non-response rate, 95% CI, 80% of power and significant value of 0.05.

| Examples                                 | Sample Size: X-Sectional, Cohort, & Randomized Clinical Trials |        |                |
|------------------------------------------|---------------------------------------------------------------------------|--------|----------------|
| Help                                     |                                                                           |        |                |
| Two-sided significance level(1-alpha):   |                                                                           |        | 95             |
| Power(1-beta, % chance of detecting):    |                                                                           |        | 80             |
| Ratio of sample size, Unexposed/Exposed: |                                                                           |        | 1              |
| Percent of Unexposed with Outcome:       |                                                                           |        | 36             |
| Percent of Exposed with Outcome:         |                                                                           |        | 55             |
| Odds Ratio:                              |                                                                           |        | 2.2            |
| Risk/Prevalence Ratio:                   |                                                                           |        | 1.5            |
| Risk/Prevalence difference:              |                                                                           |        | 19             |
|                                          | Kelsey                                                                    | Fleiss | Fleiss with CC |
| Sample Size - Exposed                    | 109                                                                       | 108    | 118            |
| Sample Size-Nonexposed                   | 109                                                                       | 108    | 118            |

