## **Phase 3: Implementation and Effectiveness Measurement**

The final phase involves the intervention implementation and evaluating its effectiveness through a randomised control trial (RCT):

1. **Study Design:** A cluster RCT will be used to compare the effectiveness of the **InTroDuce-Programme** (intervention group) versus standard care (control group) in improving the future vaccine uptake.
2. **Outcome Measurement:**
3. The module's effectiveness will be assessed using pre- and post-intervention questionnaires:
  1. **Primary Outcome:** Improvement in participants' knowledge of vaccination safety, benefits, and future uptake intentions.
  2. **Secondary Outcomes:** Identification of barriers to vaccination uptake and socio-demographic factors influencing outcomes.

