### **3.9 Statistical Analysis Plan**

#### **Statistical Methods:**

- a. Primary outcome (knowledge score) will be analyzed using paired t-tests or Mann-Whitney U tests for non-parametric data.
- b. Secondary outcomes (vaccination uptake which is yes or no) will be analyzed using multiple logistic regression to determine the factors associated with no vaccination uptake intention.

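### Section 3.9 specifies no between-arm analysis of future uptake intention, although objective 4 asks for one and the sample size rests on a two-arm difference in proportions

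*Protocol*

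**What the plan says.** Section 2.0 lists two separate aims for uptake. Specific objective 4 is about effectiveness: "To determine the effectiveness of the InTroDuce-Programme in improving knowledge and future uptake of influenza and Tdap vaccination among pregnant mothers". Specific objective 5 is about risk factors: "To determine the factors associated with low future uptake of vaccine with socio-demographic factors (age, race, income, education) among pregnant mothers".

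Section 3.5, Phase 3, describes a cluster trial comparing the programme "versus standard care (control group) in improving the future vaccine uptake". It defines the primary outcome as "Improvement in participants' knowledge of vaccination safety, benefits, and future uptake intentions", so intention is part of the primary outcome there.

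Section 3.4 sizes the trial on a "proportion of 55% in intervention group (website with vaccine information) and 36% in control group (usual care"), giving 216 before inflation, 281 after a design effect of 1.3, and 351 after 20% non-response.

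Section 3.9 has two items. Item (a) reads "Primary outcome (knowledge score) will be analyzed using paired t-tests or Mann-Whitney U tests for non-parametric data". Item (b) treats uptake as a secondary yes/no outcome that "will be analyzed using multiple logistic regression to determine the factors associated with no vaccination uptake intention".

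**The concern.** Item (b) fixes both a method and a purpose, and that purpose belongs to objective 5. Item (a) covers only the knowledge score. Objective 2 asks only for a prevalence following the programme. Nothing is left to answer the uptake half of objective 4.

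An analyst who follows section 3.9 as written can report which women do not intend vaccination without reporting whether the programme changed intention. If the comparison is added after the data are seen, the choice of vaccine, adjustment and clustering method becomes post hoc.

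There is a secondary risk for objective 5. Arm is assigned by clinic, with two clinics per arm, so the arms can differ by chance in age, race, income or education. If the programme works and arm is not in the factor model, part of its effect may be attributed to those factors.

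**Working it through.** **1. Objectives against stated analyses**

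| Question | Where asked | Analysis in 3.9 |
|---|---|---|
| Programme effect on knowledge | Objective 4; 3.5 Phase 3 | (a), knowledge score |
| Programme effect on uptake or intention | Objective 4; 3.5 Phase 3; matches the binary form of 3.4 | none stated |
| Factors for low uptake | Objective 5 | (b), logistic regression |

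**2. What the sample size is built for.** Inputs from section 3.4: p1 = 0.36, p2 = 0.55, two-sided alpha 0.05, power 80%, ratio 1:1.

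- n per arm = [1.96·√(2·0.455·0.545) + 0.8416·√(0.36·0.64 + 0.55·0.45)]² / 0.19² = 106.6, rounded up to 107. The protocol's Fleiss figure is 108.
- 216 × 1.3 = 280.8, taken as 281. Then 281 / 0.80 = 351.25, stated as 351.

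The figure reproduces within rounding, so the trial is sized for a between-arm comparison of a binary outcome. The only binary-outcome analysis in 3.9 is the factor regression.

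**3. Size of the unspecified contrast**

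- Risk difference: 0.55 − 0.36 = 0.19.
- Odds ratio: (0.55/0.45) / (0.36/0.64) = 2.17. The protocol prints 2.2.
- With 281 evaluable (140.5 per arm) and design effect 1.3, SE = √[1.3·(0.36·0.64 + 0.55·0.45)/140.5] = 0.0665.
- Normal-approximation 95% CI: 0.19 ± 1.96·0.0665, about 6 to 32 points. For the odds ratio, about 1.26 to 3.75.
- Normal-approximation power: 80.5%.

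**4. The same contrast with four clinics.** A comparison of two clinics with two has 4 − 2 = 2 degrees of freedom, or 1 if the urban/suburban stratum is also fitted. Noncentrality = 0.19 / 0.0665 = 2.86.

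| Reference distribution | Critical value | Power | 95% CI half-width |
|---|---|---|---|
| Normal | 1.96 | about 80% | 13 points |
| t, 2 df | 4.30 | about 36% | 4.30 × 6.65 = 29 points |
| t, 1 df (with stratum) | 12.7 | about 18% | 12.7 × 6.65 = 84 points |

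**5. Arm and clinic in one model.** Clinic determines arm. A design with an intercept, an arm indicator and three clinic indicators has 5 columns but rank 4 over four clinics, so arm cannot be estimated next to fixed clinic terms.

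**The case against.** **Item (b) lists no covariates, so arm could be one of the factors.** This stands as far as it goes. A reader might infer that the programme effect on intention will never be estimated. The text supports only that it is never specified: nothing requires arm in the model and nothing excludes it.

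**Model terms are commonly left to a separate analysis plan.** This is fair for baseline intention, stratum and clinic, whose absence is not a fault in itself. It does not cover the main point, because item (b) is not silent. It states a purpose, and that purpose answers a different objective.

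**Section 3.4 does not name the outcome behind 55% and 36%.** Correct. That it is uptake is inferred from the binary form and from the title of the cited web-based trial, whereas this trial measures intention by questionnaire. The mismatch between objective 4 and 3.9(b) does not depend on this inference.

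**The factor model is not shown to be biased.** Also correct. A reader might infer from section 3.1 that socioeconomic and educational factors differ by clinic and so by arm. That section also says the clinics are geographically and demographically similar, and it does not say whether the variability lies between or within clinics. Allocation puts one urban and one suburban clinic in each arm. Confounding through chance imbalance is possible, but its size is unknown. The documents give no factor effects with which an arm effect could be compared.

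**Section 3.9 calls uptake secondary.** It does, but section 3.5 places intention in the primary outcome, and a secondary effectiveness outcome would still need a between-arm analysis.

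**Conclusion.** The point holds as a failure to specify. The protocol poses an effectiveness question about future uptake, sizes the trial on a two-arm difference in proportions, and then fixes for uptake only a regression that serves the risk-factor objective. On the planning figures the unspecified contrast is 19 points, odds ratio 2.17, assuming that 55% and 36% refer to uptake and carry over to intention.

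Confounding of the demographic odds ratios is a risk if arm is omitted, not an established bias.

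This must be corrected before analysis because a headline objective has no stated analysis. The power figures (80.5% by normal approximation, about 36% on 2 degrees of freedom) assume 281 evaluable women and the protocol's design effect of 1.3. The first is an upper figure because it ignores the small number of clinics.

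**What to change.** Split section 3.9(b) in two.

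1. **Objective 4.** State a between-arm comparison of intention at one month, reported separately for influenza and Tdap, with study arm as the main term. Adjust for baseline intention where the pre-intervention survey collects it. Report a risk difference or odds ratio with a 95% CI, from an analysis that respects clinic clustering. Say how the two vaccine results will be read together, since there are then two comparisons.
2. **Objective 5.** Keep the factor model (age, race, income, education) and account for arm. Use either arm plus urban/suburban stratum with clustering handled, or fixed clinic effects, which absorb arm. Do not fit both arm and fixed clinic terms.

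Also reconcile sections 3.5 and 3.9 on whether intention is part of the primary outcome, and name in section 3.4 the outcome behind 55% and 36%.

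**Cost.** No new visit is needed, because sections 3.6 and 3.8 already provide a pre-intervention survey and a one-month assessment of intention. The change is wording, but it has a downside that the protocol should state: with four clinics, clinic-level inference has about 2 degrees of freedom, the interval will be wide (about ±29 points on the planning inputs), and power is about 36%, not 80%. Fitting the stratum as well would leave 1 degree of freedom and about 18% power.

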### **3.10 Risk and benefit to study participants**

Risk: There is minimal risk for participants.

1. Participants may feel uncomfortable answering survey questions about their attitudes or beliefs regarding vaccination and inconvenience due to the time required for surveys. However, surveys will be conducted in a nonjudgmental and private setting, with participants free to withdraw at any time.
2. Participants who choose to get vaccinated as recommended might experience common side effects such as mild fever, soreness at the injection site. However, participants will be informed of possible side effects and how to manage them.

#### **Benefits:**

1. Participants in the intervention group will gain valuable knowledge about influenza and Tdap vaccination, potentially increasing their confidence and willingness to vaccinate.

2. By choosing vaccination during the study, participants may lower their own risk of severe influenza or pertussis and protect their newborns.
3. Participants contribute to improving the understanding of barriers and facilitators of vaccination, which could benefit future pregnant women and public health programs.

### **3.11 Risk Benefit Assessment**

As stated above, there is minimal risk from the InTroDuce-Programme (web-based educational module). Study findings shall potentially improve outcomes of participants and future pregnant women. The expected benefit outweighs the minimal risk to participants.

### **3.12 Ethics of Study**

Ethical approval will be obtained from the National Medical Research Registry and Ethics Committee. Permission will be obtained from the Selangor State Health Department and Hulu Langat district office before data collection. Study will be conducted in compliance with ethical principles outlined in the Declaration of Helsinki and Malaysian Good Clinical Practice Guideline.

Pregnant women are included in this study as they are the primary population at risk for influenza and pertussis complications. Vaccination during pregnancy is critical for protecting both the mother and baby from these preventable illnesses. Therefore, their inclusion is essential to understand barriers and improve vaccination uptake in this vulnerable group, which aligns with public health goals.

- ☐ Participants will be provided with detailed information about the study, including its purpose, procedures, potential risks, and benefits.
- ☐ Written informed consent will be obtained, ensuring they understand their voluntary participation and right to withdraw at any time without penalty or impact on their standard care.
- ☐ The intervention involves an educational program, which poses minimal risk. No invasive procedures will be conducted as part of this study.
- ☐ Participants with contraindications to vaccination (e.g., severe allergic reactions) will be excluded from the study to ensure safety.

### **3.13 Informed Consent/Assent Process**

Patients shall be informed of the study during their usual clinic visits. If they are willing to participate, the consent forms will be signed and dated. If they need to, they are allowed to take the information sheet home to consult with their family members, and another day for getting consent arranged.

### **3.14 Privacy and Confidentiality**

Participants' names will be kept on a password-protected database and will be linked only with a study identification number for this research. The identification number instead of patient identifiers will be used on participant data sheets. Access to participants' data will be restricted to the study researchers through a password-protected database. The data will be securely stored for a minimum of seven years following the study's completion, after which it will be permanently deleted. Participants will not be allowed to view their personal study data, as the data will be consolidated into a database.

### 3.15 Conflict of Interest

The investigators declare they have no conflict of interest.

### 3.16 Publication Policy

No personal information will be disclosed and subjects will not be identified when the findings of the survey are published. Permission from the Director General of Health, Malaysia will be obtained prior to publication.

### 3.17 Termination of Study

The researchers may decide to terminate the study at any time. Participants will be informed if the study is terminated and follow-up visits will be arranged if needed.

